### Participants, recruitment, randomization, and statistical power analysis

HCWs (*n* = 140) with the presence of symptoms of chronic pain will be recruited across Oregon, Washington, and Idaho to participate in this study with the help of our partner organizations: the Oregon Home Care Commission, the Service Employees International Union (SEIU) 775 Benefits Group in Washington, and the St. Luke’s Health System in Idaho. We will perform 1:1 randomization of block size 2 within each state. The randomized groups will be computer generated by the study statistician and kept in sealed envelopes.

The effectiveness and implementation of COMPASS-NP will be evaluated using a mixed-methods hybrid type II evaluation approach [52]. In this cluster randomized waitlist control design, all HCWs will participate in the trial for 20 weeks, with measures collected by online surveys at baseline, 10 weeks (follow-up 1), and 20 weeks (follow-up 2) (Fig. 1). Fourteen groups of 10 workers each will be created based on residence in the same state and schedule availability for attending group meetings. Half of the recruited groups in each state will be randomly selected to complete the intervention during the first 10 weeks, while the remaining groups serve as wait-list controls (i.e., delayed start) during the same period. After 10 weeks, the wait-list groups will initiate the intervention and finish at week 20. Original intervention participants will experience usual practice during weeks 10 to 20. A randomized waitlist study design was chosen because it creates an intervention vs. control group comparison but also permits every participant to eventually receive the intervention. Given our focus on a vulnerable population in high need of interventions, we deemed this to be the best and most ethical approach for our project.

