**Fig. 1 Fig1:**
[figure not shown]
Participant timeline

The sample size target of 140 (70 in the intervention group, 70 in the waitlist control group) was based on an a priori power analysis to achieve 80% power to detect a moderate effect size (*d*= 0.50) between the groups at 10 weeks on our primary outcomes. Our sample size requirement assumes a conservative 20% attrition at each time point (original COMPASS study saw 15% attrition at 12 months) [27]. We also assumed an AR(1) correlation structure with rho = 0.7 for repeated observations within each worker. The power calculation also takes into account a conservative intracluster correlation coefficient within each virtual group of 0.10 (in the original COMPASS trial, ICC range was 0.001–0.086) [27]. The estimated effect size of *d* = 0.50 is the average effect size for safety changes at 6 months in the original COMPASS trial, which represents a reasonable estimated effect for COMPASS-NP for pain-related limitations outcomes.

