### Data analysis, storage and fidelity

#### Quantitative data analysis

We will summarize participant demographics using descriptive statistics and data visualizations (e.g., histograms, scatter plots) to evaluate the differences between study arms. Effectiveness analyses will employ an intent-to-treat approach where participants are analyzed and included according to their randomized condition [77], regardless of their degree of intervention participation. This approach also utilizes all available data from participants across all time points. To test our hypothesis that the intervention group will experience reduced pain interference with work and life, we will evaluate the within- and between-group differences in the magnitude of change in the two primary outcome domains, using a difference-in-differences (DID) approach that suits the between-group and within-group design of this study. The DID approach is a general approach that can estimate relative changes in outcomes within-group and between study groups through a group-by-time interaction group. Specifically, we will implement our DID approach using generalized linear mixed models (GLMM) [78], which offer flexible regression modeling to accommodate for different sources of correlations (e.g. serial and intra-group), categorical and continuous covariates, and fixed and time-dependent covariates. These GLMMs offer a wide range of parametric distributions to model the dependent variables, including logistic regression (binary data), beta regression (percent data), Poisson regression (count data), and Gaussian regression (normally distributed data). For example, to assess the changes in pain interference, a Gaussian linear mixed model can analyze pain interference at baseline, week 10, and week 20 as a function of whether a HCW belongs to the intervention condition, time, the interaction of condition and time, and other potential confounders (e.g., psychosocial factors from our background survey). We will operationalize comparisons by computing interaction contrasts on pre/post-intervention differences within and across groups. Intervention group membership will be the between-subjects factor and pre/post-intervention assessment scores on primary outcomes will be the within-subjects factors. The interaction contrast approach will allow us to efficiently compare the 2 study arms at the end of 10 and 20 weeks on each pain interference measure with a focused, one degree of freedom hypothesis test. Additionally, to take advantage of the full longitudinal data set (baseline, 10- and 20-week time points), we will implement an analysis of response profiles to characterize the patterns of change in the mean response over time in the two arms by treating time as a categorical factor. Our approach will include random effects for virtual group clusters to account for the correlation of outcomes within virtual groups. We will also include random effects for HCWs to account for the correlation of observations within a worker over time. Depending on the distribution of the outcomes of interest, standard errors may be difficult to estimate using standard regression variance output. Thus, if we cannot accurately represent standard errors, we plan to implement bootstrapping to obtain reliable standard errors when appropriate. If imbalances in participant characteristics are observed at baseline, we will consider propensity score weighting to improve efficiency [79]. We will explore missing data and apply standard practices to control for the differences between subjects in missing data or to impute scores if non-trivial levels of missing data are observed. Similar analytic methods will be applied to secondary outcomes, with appropriate adjustments based on the characteristics of the data and distributions. We will follow the CONSORT 2010 guidelines when reporting study results [80].

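### If the virtual-group random effect is an intercept only, clustering that develops once groups meet is missing from the standard error of the week-10 difference-in-differences contrast

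*Protocol article*

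**What the plan says.** Under *Quantitative data analysis*, the article plans difference-in-differences estimates from mixed models at baseline, week 10 and week 20. The arms are compared by interaction contrasts, each "with a focused, one degree of freedom hypothesis test". Two random terms are named. For groups: "Our approach will include random effects for virtual group clusters to account for the correlation of outcomes within virtual groups". A separate worker term is given the task of handling correlation over time. No group-by-time term is named, and the group term is not said to be an intercept only. Bootstrap standard errors are allowed where the outcome distribution makes model-based ones unreliable; the resampling unit is not stated.

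Under *Participants, recruitment, randomization, and statistical power analysis*, 14 groups of 10 are formed by state and schedule. Half start at once, "while the remaining groups serve as wait-list controls (i.e., delayed start) during the same period". The target of 140 is meant "to achieve 80% power to detect a moderate effect size" (d = 0.50) "between the groups at 10 weeks on our primary outcomes". "The power calculation also takes into account a conservative intracluster correlation coefficient within each virtual group of 0.10", and the earlier trial's range is given as 0.001 to 0.086. Repeated measures are assumed AR(1) with rho 0.7. "Our sample size requirement assumes a conservative 20% attrition at each time point".

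**The concern.** A group effect that is equal at baseline and week 10 drops out of each worker's change, so it contributes nothing to the error of the contrast. That is harmless for correlation already present at baseline, such as shared state or similar schedules. Here, however, the groups are newly formed, and the main source of correlation is what follows: shared meetings, peer leaders, a common facilitator and group goals. By week 10 only the intervention groups have had these. Correlation of that kind is group-by-time variance, and an intercept cannot carry it. If it exists and is left out, the confidence intervals and p-values for both primary measures are too optimistic.

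**Working it through.** **Inputs from the article.** 7 groups per arm; 10 workers per group, so 8 completers at week 10 after 20% loss, or 56 per arm; rho 0.7; ICC 0.10; d = 0.50; power 80%.

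**Assumptions.** Two-sided 5% (no level is stated); outcome variance 1 at each visit. Let g be the share of outcome variance that arises from the group after baseline, in the intervention arm only at week 10. The article gives no value for g, so a range of 0 to 0.10 is shown.

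**1. The planned sample size.** The formula is not printed. A baseline-adjusted variance with a full design effect comes close:

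- variance factor (1 - 0.7²) = 0.51; design effect 1 + 7 × 0.10 = 1.7
- completers per arm: 2 × (1.960 + 0.842)² × 0.51 × 1.7 / 0.50² = 54.5, so 55
- recruited per arm: 55 / 0.8 = 68.75, so 69; total 138 against the stated 140

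The target is therefore consistent with charging the full ICC to the week-10 comparison.

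**2. Cancellation.** Write a worker's outcome as fixed part + group intercept b + worker intercept w + residual e. The change from baseline to week 10 contains neither b nor w. If a further group effect c (variance g) appears only at week 10 in groups that have met, the change contains c, shared by the 8 workers in that group.

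**3. Two-visit analysis.** The change variance is 2(1 - 0.7) = 0.6. The model's standard error is √(2 × 0.6/56) = 0.146. The true variance is larger by D = 1 + ½ × 7 × g/0.6; the ½ enters because one arm only is affected. Type I error = 2[1 - Φ(1.96/√D)]. At g = 0.10, D = 1.583, the true standard error is 0.146 × 1.258 = 0.184, and the error rate is 11.9%.

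**4. Three-visit model with worker and group intercepts.** Under AR(1) the three pairwise correlations are 0.7, 0.7 and 0.49, mean 0.63. A random-intercept model treats them as equal, so it takes the change variance as 2(1 - 0.63) = 0.74 instead of 0.6, and its standard error is √(2 × 0.74/56) = 0.163. Type I error = 2[1 - Φ(1.96 × √(0.74/0.6)/√D)].

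| g | D | Two-visit: formula (simulation) | Three-visit: formula (simulation) | Group means, 12 df (simulation) |
|---|---|---|---|---|
| 0 (constant clustering) | 1.000 | 5.0% (5.1%) | 3% (3.1%) | 5.2% |
| 0.02 | 1.117 | 6.4% (5.9-6.8%) | 3.9% (3.7-4%) | 4.5% |
| 0.05 | 1.292 | 8.5% (8.5-8.9%) | 5.5% (5.5-5.8%) | 5.1% |
| 0.086 | 1.502 | 11.0% (11.1%) | 7.6% (7.7%) | 5.3% |
| 0.10 | 1.583 | 11.9% (11.7-12.3%) | 8.4% (8.4%) | 5.3% |

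With all 10 workers per group retained, simulation gives 9.8% and 14.5% (two-visit) and 6.2% and 10.1% (three-visit) at g = 0.05 and 0.10.

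**5. Power after correction.** For the 7 versus 7 comparison of group-mean changes (14 - 2 = 12 df) at d = 0.50 with 8 completers per group, simulated power is about 88% at g = 0, 79% at 0.05 and 71% at 0.10.

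**The case against.** The article does not say that the group effect is constant over time. It speaks of random effects in general and says that mixed models can handle both serial and intra-group correlation. The covariance structure may be set out in an analysis plan that is not shown. This stands, and it makes the point conditional. What remains is that the article commits to a contrast, names one group term, and ties time only to the worker term; a reader who fitted the model from this text would fit an intercept.

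The size of g is not in the documents. The ICC of 0.10 is called conservative, and the earlier range starts at 0.001. Groups share state and schedule, so part of any ICC may already exist at baseline, and that part cancels properly. This also stands.

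The three-visit model that the article gives as its example has lower error rates. That is true, but only because equal correlations overstate the baseline-to-week-10 change variance when AR(1) holds. One misspecification offsets another, and modelling the AR(1) structure assumed in the power paragraph would remove the offset.

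A reader might also infer that the power paragraph and the analysis contradict each other. They do not. Charging an ICC and then using a contrast from which a constant group effect cancels is merely conservative: the design would have 93-95% power, and 86 to 96 workers would be enough.

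The bootstrap is a partial answer. It is triggered by the outcome distribution, and resampling workers instead of groups would repeat the omission.

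**Conclusion.** The point holds in conditional form. If the group term is a random intercept, clustering that develops during the meetings is not in the standard error of the primary contrast. With g between 0.05 and 0.10 in the meeting arm, 8 completers per group and an assumed two-sided 5% level, type I error is about 9-12% for a two-visit analysis and about 5.5-8.5% for three visits with random intercepts under AR(1) 0.7. With constant or very small clustering it is near or below 5%. It would go too far to say that the planned test runs at 9-12%, or that the plan fixes a time-constant group effect: the documents give neither the split of the ICC into constant and developing parts nor the structure of the random effect. The point is still more than a missing detail, because only one arm meets before week 10 and a model that covers this case is readily available.

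**What to change.** In *Quantitative data analysis*:

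- Specify a group random intercept plus a random group-by-time effect, keep the worker terms, and test the week-10 contrast with cluster-level degrees of freedom (about 12). The degrees of freedom alone are not enough: a 12-df reference without the extra variance term still gives about 8-9% at g = 0.10 in the two-visit setting.
- If the group-by-time variance cannot be estimated, compare the 7 versus 7 group-mean changes. The error rates and power reported after correction were simulated for this comparison. The group-by-time mixed model was checked only for its standard error, in a small run of 84 simulated trials (mean 0.197 against an empirical 0.189, versus 0.148 for intercepts only).
- State that any bootstrap resamples whole groups.

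The cost is a few sentences and a wider interval. The sample-size reconstruction implies a standard error of √(2 × 0.867/56) = 0.176 (0.867 = 0.51 × 1.7), while the true value at g = 0.10 is 0.184 before allowing for 12 df, so the extra width is not fully covered by the present sample size. Power falls to about 79% (g = 0.05) or 71% (g = 0.10). No new data or participants are needed.

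### Propensity weighting triggered by chance baseline imbalance is not a dependable route to efficiency; pre-specified adjustment for the baseline outcome and state is

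*Protocol article*

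**What the plan says.** The Quantitative data analysis section of the protocol article sets out an intention-to-treat difference-in-differences analysis by mixed model, with random effects for virtual group and for worker. The effect is a one-degree-of-freedom group-by-time contrast. Baseline characteristics are to be summarised "to evaluate the differences between study arms". The section then adds: "If imbalances in participant characteristics are observed at baseline, we will consider propensity score weighting to improve efficiency". It gives no imbalance measure or threshold, and does not say whether a weighted or an unweighted result would be primary. The covariates of its example model are left open.

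The sample size is set out under Participants, recruitment, randomization, and statistical power analysis: "The sample size target of 140 (70 in the intervention group, 70 in the waitlist control group"), "based on an a priori power analysis to achieve 80% power to detect a moderate effect size" of d = 0.50. It assumes a "conservative intracluster correlation coefficient within each virtual group of 0.10", an AR(1) "correlation structure with rho = 0.7 for repeated observations within each worker", and 20% attrition at each time point. The same section randomises groups 1:1 in blocks of two within state.

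**The concern.** The sentence joins a trigger (observed imbalance) to a purpose (efficiency), and the two do not belong together. In a randomised comparison the unadjusted contrast is unbiased over repeated allocations. A covariate improves precision to the extent that it predicts the outcome. A strongly prognostic variable is worth adjusting for even if it is balanced, and a non-prognostic one is not worth weighting on even if it is imbalanced. A trigger based on imbalance therefore selects on the wrong property.

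Two things are at stake. First, whether the effectiveness analysis is weighted would depend on a look at chance differences that will often be present. Second, the variable most likely to bring precision, the baseline value of the outcome, is already collected, but a change contrast uses it less efficiently than it could.

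**Working it through.** **Inputs.** From the power section: 70 per arm, 14 groups of 10, ICC 0.10, within-worker correlation 0.7, 20% attrition, d = 0.50. At week 10 this leaves 8 per group and 56 per arm, with design effect 1 + (8 − 1) × 0.10 = 1.7. The article does not state alpha; 0.05 two-sided is assumed.

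**Reproducing the sample size.** Two independent means with d = 0.50 and 80% power need 2 × (1.960 + 0.842)² / 0.5² = 62.8, so 63 per arm. With baseline adjustment the variance factor is 1 − 0.7² = 0.51, and 63 × 0.51 × 1.7 / 0.80 = 68.3, so 69 per arm against the stated 70. The stated figure reproduces.

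**Power at 56 completers per arm.** SE = √(2 × factor × 1.7 / 56), and normal-approximation power = Φ(0.5/SE − 1.960).

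| Analysis | Variance factor | SE | Power, normal | Power, t on 12 df |
|---|---|---|---|---|
| Week-10 score alone | 1.00 | 0.246 | 52.8% | not needed |
| Change contrast | 2(1 − 0.7) = 0.60 | 0.191 | 74.5% | 67% |
| Baseline-adjusted | 1 − 0.7² = 0.51 | 0.176 | 81.1% | 74% |

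The 12 degrees of freedom are 14 groups minus 2 arms. Of these variants, only the baseline-adjusted one with the normal approximation reaches the stated 80%. A group-by-time contrast whose baseline means are free to differ between arms corresponds to the change row when data are complete.

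**How often imbalance would be seen.** The Quantitative data section lists about 12 demographic and background items and 5 psychosocial factors, so 12 to 17 characteristics, treated here as independent. With 70 per arm the standardised difference has SE √(2/70) = 0.169.
- Absolute difference above 0.25: 2 × (1 − Φ(0.25/0.169)) = 13.9% for each characteristic. At least one: 1 − 0.861¹² = 83% and 1 − 0.861¹⁷ = 92%. With a covariate ICC of 0.05 and 10 per group (design effect 1.45), the figure for 12 characteristics rises to 95%.
- A p < 0.05 rule: 1 − 0.95¹² = 46% and 1 − 0.95¹⁷ = 58%.

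**What weighting does to precision.** Trials of 14 groups of 8 with ICC 0.10 were simulated, using inverse-probability weights from a logistic propensity model. R² is the share of outcome variance that the covariates explain.

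| Covariates | Variance, weighted / unweighted |
|---|---|
| 3 to 15, R² = 0 | 1.02 to 1.19 |
| 3 to 15, R² = 0.10 | 0.94 to 1.09 |
| 3 to 15, R² = 0.25 | 0.80 to 0.94 |
| 3 to 15, R² = 0.50 | 0.55 to 0.72 |

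As single points, 12 non-prognostic covariates gave about 1.17 and 5 covariates at R² = 0.25 gave about 0.82. Runs differ by a few points: another run of 3,000 trials gave 1.13 to 1.14 and 0.85. The direction is stable, and it follows prognostic strength and the number of covariates, not imbalance.

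**The case against.** The best defence is that weighting in a randomised trial can improve precision, so the stated aim is legitimate. The psychosocial items were chosen because they relate to pain and may well be prognostic. In the simulation weighting came close to regression adjustment (0.83 to 0.85 against 0.82 to 0.84 for 5 covariates at R² = 0.25). A propensity model that included the baseline outcome would recover much of the same gain. All of this stands. A reader might infer that weighting lowers power as a rule; the figures above do not support that, since variance fell in every scenario with R² of 0.25 or more.

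The wording is also only an intention to consider, and an analysis plan that is not shown may fix the covariates, the metric and the status of a weighted result. Their absence from an article is not the complaint. What the article does state is the link between imbalance and efficiency, and that link is mistaken however the details are settled.

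A reader might also infer an inflated type I error from choosing between weighted and unweighted results. The document does not support this: the trigger is baseline characteristics, and nothing proposes selecting a result by its significance. Nor can one say that imbalance would almost always be declared. That depends on the rule; at p < 0.05 it is close to an even chance.

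**Conclusion.** The concern holds in a limited form. Imbalance-triggered weighting is a poorly aimed way to gain efficiency: it may raise or lower precision, depending on covariates that the article does not name. Pre-specified adjustment for the baseline outcome is dependable. It cuts the variance factor from 0.60 to 0.51, a 15% reduction (0.09/0.60), worth about 81% against 75% power by normal approximation, or 74% against 67% with t on 12 degrees of freedom.

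These figures rest on the plan's own ICC, correlation and attrition, on an assumed two-sided 5% level, on equal group sizes, and on the same design effect for both analyses. The imbalance probabilities assume independent characteristics. The simulation compares estimators directly and does not fit a weighted mixed model. That the baseline-adjusted formula reproduces the sample size does not prove that the plan used it, but it does show that the stated power needs that precision.

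**What to change.** Replace the sentence on imbalance and weighting with one primary model fixed in advance. It should adjust for the baseline value of the outcome, or equivalently constrain the baseline means of the two arms to be equal in the longitudinal model. It should include state, the randomisation stratum, and at most a few named prognostic covariates, and apply whatever imbalance is observed. If propensity weighting is kept, specify it in advance and label it a sensitivity analysis.

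The cost is wording in the protocol and analysis plan; all the variables are already collected. Fitting three states as fixed effects uses two group-level degrees of freedom (from 14 − 2 = 12 to 14 − 4 = 10), which is a reason to keep any group-level terms few.

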
#### Mixed methods analysis

The interpretation of qualitative data from interviews will be considered in the context of quantitative data (intervention effectiveness results, intervention process/implementation statistics, HCW intervention acceptability ratings), as well as feedback, correspondence, and materials gathered from study partners throughout the study. This evaluation in context will illustrate the fit and feasibility of COMPASS-NP within states’ training models and HCW population. We will use these findings, combined with quantitative intervention effectiveness data to descriptively assess systems for replicating/replacing ergonomic tool vouchers, as well as between-system/state differences that may impede or encourage intervention accessibility, appropriateness, and adoption.

